#### Calculation of the sample size

The calculation of the sample size for this study uses a conservative procedure to identify a 10% reduction in dating violence prevalence on the intervention group compared to the control group. Adopting a significance level of 5%, a testing power of 80%, and a 50% dropout rate over the course of the study, it was calculated that each condition should have 610 individuals.

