## Background

Violence received from and practiced against a romantic partner is widespread among Brazilian adolescents. Evidence shows that eight of every ten adolescents (age 15 to 19) have already been victims of or have practiced some type of aggression against an intimate partner at some point in their lives, particularly of a sexual or emotional nature [1]. The predominant constructs of femininity and masculinity contribute to the normalization of dating violence and make its recognition difficult among Brazilian adolescents, as violent manifestations are taken as expressions of love or playfulness inherent to intimacy [2, 3]. This violence invisibility impedes help-seeking and sustains victimization and perpetration of violence by intimate partners in adolescence. Findings of a national study show that adolescents rarely seek help when they are victims of their intimate partner, but when they do so, they prioritize friends and family as the sources while professional help is sought less often [4].

Effective prevention and early intervention services aimed at this type of violence in the adolescent public [5] as well as studies with these purposes are lacking. Results of an evaluation of the implementation quality a law aimed at the eradication, prevention, and punishment of domestic violence against women (the Maria da Penha Law), reveal that educational actions focused on prevention of violence in adolescents, boys or girls, are rare [6]. The paucity of preventive services identified in public policies is also reflected in research. As opposed to other countries in the Americas, which produce frequent research on the prevention of dating violence among adolescents, there is a scarcity of evidence-based prevention interventions in Brazil [7].

Recent Brazilian interventions against partner violence are offered face-to-face in the school environment and conducted in a workshop format by previously trained facilitators [8–12]. Evidences has pointed reduction in sexist and homophobic beliefs [8] and dating violence perpetration [10], increasing in emotion regulation skills [9], and intervention’s acceptability [11, 12]. Even with their promising results, such interventions require institutional support, space in the school’s curriculum schedule, and qualified personnel for their execution in new contexts, all of which hinder their diffusion at a national level resulting in limited public health impact.

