### Statistical analysis

Descriptive statistics will be used to describe the characteristics of the participants in the baseline and usability data. The principal analyses will consist of intra- and intergroup comparisons between the baseline and the three-month follow-up on the outcomes of victimization and perpetration of physical, psychological, and sexual violence; quality of the romantic relationship; and conflict management skills. Multivariate analysis of covariance will be used to examine the efficacy of the intervention on these outcomes. The attachment style and the relationship’s violence status will be used as covariates. In addition to this, intergroup comparisons will be conducted using the *t*-test on the three-month follow-up outcome of seeking help. Moderation analysis will be employed to evaluate the differential effects of the intervention based on gender, age, and sexual orientation. A significance level of 0.05 will be adopted.

Omitted or incomplete data will be handled via multiple imputation using the Missing Value Analysis procedure of SPSS Statistics. Intention-to-treat analyses will be carried out, and all randomized participants will be posteriorly included regardless of having completed the intervention or not. The effects of Dating SOS will be estimated utilizing Cohen’s d (where values around 0.2 = small effect size; around 0.5 = medium effect size; and around 0.8 = large effect size).

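### The stated 80% power with 610 per arm cannot be verified, and on the natural conservative reading (50% vs 40%) it holds only for a one-sided test; two-sided power is about 70%

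*Protocol article*

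**What the plan says.** The Calculation of the sample size section of the protocol article says that the calculation "uses a conservative procedure to identify a 10% reduction in dating violence prevalence on the intervention group compared to the control group". Its other inputs are given as "Adopting a significance level of 5%, a testing power of 80%, and a 50% dropout rate over the course of the study", and the result is 610 per condition. The Participants and design section doubles this to 1220, divided evenly.

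Three inputs are not stated there: the control-arm prevalence, whether the 10% is absolute or relative, and whether the 5% is one- or two-sided. The Statistical analysis section adds only "A significance level of 0.05 will be adopted" and plans a multivariate analysis of covariance for the efficacy outcomes.

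The one prevalence figure that could bear on the calculation is in the Background, that "eight of every ten adolescents (age 15 to 19) have already been victims of or have practiced some type of aggression". The sample size section does not refer to it.

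**The concern.** A two-proportion sample size needs a control rate, an effect on a defined scale, and a sidedness. The section publishes a result and a power without them, so a reader has to supply them.

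The word conservative points most naturally to a prevalence near 50%, where the variance of a proportion is greatest. On that reading 610 is too small for a conventional two-sided 5% test at 80% power, but it is exactly right for a one-sided one. A one-sided test is declared nowhere, and the planned multivariate test is non-directional. The intervention pre-testing section also reports professionals' worry about side-effects in already violent relationships, and a one-sided efficacy test would not look for harm.

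At stake is how a null result is read. If true power is 70%, the chance of missing the target effect is 30% rather than the advertised 20%.

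**Working it through.** **Inputs from the protocol article:** significance level 5%, power 80%, dropout 50%, 1:1 allocation, 610 per arm. Completers per arm: 610 × (1 − 0.5) = 305.

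**Assumed, because not stated:** control prevalence p1, intervention prevalence p2, sidedness.

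**Formula** (pooled variance under the null, d = p1 − p2, p̄ their mean):

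n per arm = [zα·√(2p̄(1−p̄)) + zβ·√(p1(1−p1) + p2(1−p2))]² / d²

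with zβ = 0.8416, and zα = 1.9600 two-sided or 1.6449 one-sided. The number to randomise is n / (1 − 0.5). The continuity-corrected size is (n/4)·[1 + √(1 + 4/(n·d))]².

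**Reproducing 610, with 50% vs 40% assumed.** Here √(2 × 0.45 × 0.55) = 0.70356 and √(0.25 + 0.24) = 0.70.

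- One-sided: (1.6449 × 0.70356 + 0.8416 × 0.70)² / 0.01 = (1.1573 + 0.5891)² / 0.01 = 304.99, so 305. Then 305 / 0.5 = **610**, exact.
- Two-sided: (1.3790 + 0.5891)² / 0.01 = 387.3, so 388. Then 388 / 0.5 = **776**. With continuity correction: 407.1, so 408, and 816 randomised.

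**Two-sided power with 305 completers, 50% vs 40%:** Φ[(0.10 × √305 − 1.3790) / 0.70] = Φ[(1.7464 − 1.3790) / 0.70] = Φ(0.525) = **70.0%**.

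**Other routes to 610**, all two-sided with the same dropout inflation:

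- 78.5% vs 68.5%, no correction: n = 304.6, so 305, so 610.
- 81% vs 71%, continuity-corrected: n = 304.8, so 305, so 610.

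The stated figure therefore does not identify its own assumptions.

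**Two-sided 5% power with 305 completers per arm, no continuity correction:**

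| Control vs intervention | Scale of the 10% | Power |
|---|---|---|
| 50% vs 40% | absolute | 70.0% |
| 55% vs 45% (lowest) | absolute | 69.6% |
| 70% vs 60% | absolute | 73.7% |
| 78.5% vs 68.5% | absolute | 80.1% |
| 80% vs 70% | absolute | 81.5% |
| 80% vs 72% | relative | 63.9% |
| 50% vs 45% | relative | 23.4% |

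For a 10-point reduction, two-sided power is below 80% at every control prevalence from about 32% to 78%. For a relative 10% reduction it is below 80% at every prevalence up to about 86%.

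**Two restatements of the 50% case.** With 305 completers per arm, the difference detectable from 50% at 80% two-sided power is about 11.2 points. Alternatively, 610 per arm gives 80% two-sided power for 50% vs 40% only if dropout is no more than 1 − 388/610 = 36.4%.

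**The case against.** The strongest reply is that power cannot be computed without a control prevalence, and the article gives none. The value 50% appears nowhere as a prevalence. Near the one figure the Background does give, about 80%, a two-sided test with correct inflation reproduces 610 and has 80% power or slightly more. The word conservative is undefined and could refer to a continuity correction or to the large dropout allowance. If a one-sided test at 50% vs 40% was meant, 610 is arithmetically correct. And this is a condensed article, so a fuller document may hold the missing inputs.

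Much of this stands. It rules out saying flatly that 610 does not give 80% power. A reader might also infer that dropout was handled by multiplying by 1.5 instead of dividing by 0.5, since the continuity-corrected two-sided size for 50% vs 40% comes close: 408 × 1.5 = 612. The document does not support that. The match is not exact, other routes reach 610 without any error, and the worksheet is not shown.

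Two parts of the reply are weaker. The 80% figure is lifetime prevalence, of victimization or perpetration of any kind, at ages 15 to 19. The trial enrols ages 15 to 29 and asks about violence in the current relationship. Planning on 80% would also not be conservative, because it needs fewer participants than 50%. And although an article may leave detail to a fuller plan, this one chose to print the power claim and call it conservative, so the claim should be checkable and true on that description.

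**Conclusion.** The point holds in conditional form, at moderate severity. The statement of 80% power with 610 per arm cannot be verified from the inputs given. On the natural conservative reading (assumed: 50% vs 40%, absolute) it is a one-sided result, and two-sided power with 305 completers is about 70%, a shortfall of 10 percentage points.

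The 80% is met two-sided for a 10-point reduction only at control prevalences of about 78.5% or more, or about 31.5% or less. If the 10% is relative, starting from 80% does not rescue it.

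These figures rest on an uncorrected comparison of two proportions among completers, with the stated 50% loss. The plan's intention to impute missing data and analyse everyone randomised does not change this materially, since imputation does not by itself recover the information lost with half the outcomes. The exact match at 50% vs 40% is good but not conclusive evidence of how 610 arose.

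**What to change.** In the sample size section, state the control prevalence, whether 10% is absolute or relative, and the sidedness actually used. Then, according to which it was:

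- **50% vs 40%:** either restate the two-sided power as about 70% with 305 completers per arm (equivalently, a detectable difference of about 11.2 points from 50% at 80% power), or declare a one-sided 5% test and make the Statistical analysis section match it.
- **A prevalence near 80%:** say so, give its basis for violence in the current relationship at ages 15 to 29, drop the word conservative, and show the power at lower prevalences.
- **A relative reduction:** give both proportions and the power that follows from them.

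This is a change of wording only, and enrolment can stay at 1220. The cost is that the power on record may become less favourable.

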#### Participants and design

An experimental design with a pre-test evaluation and three-month follow-up will be used. Youths between 15 and 29 years of age and their current partners will be invited to participate. A sample of 1220 youths, which will be randomly and evenly divided between the experimental and control groups, is expected. Participants younger than 15 and older than 29 or not currently in a dating relationship will be excluded from the intervention.

The intervention group will receive the SOS Dating intervention, while the control group will receive general information about dating violence, life skills, and sexual and reproductive rights, based on the book “Telling a night out from a trap: a Guide for the Empowerment of Teens in Intimate Relationships” (Diferenciando Baladas de Ciladas: um Guia para o Empoderamento de Adolescentes em Relacionamentos Íntimos) [48], available at http://www.geppsvida.com.br/publicacoes/cartilhas-e-guias/.

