#### Randomization

The randomization for the experimental and control group will be performed after the eligibility evaluation, the express agreement to participate in the intervention through the consent form, and the baseline evaluation. The placement into one group or the other will be performed automatically by the *TailorBuilder* software, as has been done before in other similar interventions [45, 46].

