#### Instruments and procedures

##### Eligibility evaluation

After clarifications regarding the research and declaration of voluntary participation via the consent form, the participants will answer a social-demographic survey composed of closed questions about age, gender, level of education, socio-economic level, religion, sexual orientation, parents’ professions, parents’ educations, previous dating experience, romantic status (whether single or dating), and how long have they been dating. The participants between 15 and 29 years of age who have a current romantic partner will be included in the intervention, while those who do not meet both criteria will be excluded (Fig. 2).

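### Current partners are invited too, but allocation and analysis are described only for individuals, so about half of the couples in which both members enrol would be split across arms

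*Protocol article*

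**What the plan says.** All references are to the protocol article.

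- Participants and design: "Youths between 15 and 29 years of age and their current partners will be invited to participate". The next sentence reads "A sample of 1220 youths, which will be randomly and evenly divided between the experimental and control groups, is expected".
- Eligibility evaluation: "The participants between 15 and 29 years of age who have a current romantic partner will be included in the intervention". A partner in that age range has a current partner by definition, so he or she qualifies independently.
- Calculation of the sample size: "it was calculated that each condition should have 610 individuals".
- Randomization: after eligibility, consent and baseline, "The placement into one group or the other will be performed automatically by the" tailoring software. No unit of allocation other than the participant appears.
- Victimization and perpetration of dating violence: the CADRI items ask how often violent events occurred in the current relationship, as victim and as perpetrator.
- Statistical analysis: multivariate analysis of covariance with attachment style and violence status as covariates, a t-test for help seeking, and moderation by gender, age and sexual orientation.

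No section links two partners, keeps a couple in one arm, limits entry to one member per couple, or says whether partners count towards the 1220. The Discussion names partner mutability as a limitation but does not consider that both partners may be enrolled.

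**The concern.** The primary outcomes belong to the relationship: what one partner reports as perpetration, the other reports as victimization. The Theoretical basis section expects the intervention to work through the couple, by way of better responses to the partner and less violence in both directions. If one partner receives Dating SOS and the other receives the control material, part of the benefit may appear in the control arm. The control partner may also see intervention content, because feedback is e-mailed as a PDF.

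This is a design matter, not a detail that can wait for an analysis plan. If partners are not linked at entry, they cannot be identified later, and no analysis can then separate couples with one, both or neither member treated. Without a stated unit, it is also unclear which of these effects the trial estimates.

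**Working it through.** **1. The plan's own figure.** The stated inputs are "a conservative procedure to identify a 10% reduction in dating violence prevalence on the intervention group compared to the control group" and "Adopting a significance level of 5%, a testing power of 80%, and a 50% dropout rate over the course of the study". Control prevalence, sidedness and whether the 10% is absolute are not given. Assuming 50% against 40%, a one-sided 5% test and pooled variance without continuity correction:

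n = [z(0.95)·√(2·0.45·0.55) + z(0.80)·√(0.5·0.5 + 0.4·0.6)]² / 0.10² = 305 per arm, and 305 / (1 - 0.5) = 610.

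This matches the stated 610. A two-sided test needs 388, hence 776 enrolled per arm. Other assumptions come close to 610 (80% against 70%, two-sided with continuity correction, gives 626), so the inputs are not uniquely recovered. In every variant tried, the 610 are independent individuals.

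**2. Share of couples split.** With 1220 people divided evenly and individually, the chance that a given pair lands in different arms is 610/1219 = 50.0%. This applies only to couples in which both members enrol. If a share c of participants has an enrolled partner, c/2 of all participants have a partner in the other arm: 5%, 15% or 25% at c = 10%, 30% or 50%. These values of c are assumptions, because the article gives no uptake.

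**3. How far the contrast can shrink.** Take a 10-point effect that is fully shared within the relationship.

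- *Effects add:* both treated 20, split 10 for each member, neither treated 0. Treated members average (20 + 10)/2 = 15 and control members (10 + 0)/2 = 5. The contrast is 10, so there is no dilution.
- *Second treatment adds nothing:* both treated 10, split 10 for each member, neither treated 0. Treated members average 10 and control members 5. The contrast among paired participants is 5. Over the whole sample it is 10·(1 - c) + 5·c = 10·(1 - c/2).

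The range is therefore from 10 points down to 10·(1 - c/2).

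**4. Power in the worst case.** With 305 completers per arm and 50% control prevalence (assumed):

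| c | contrast (points) | power, one-sided | power, two-sided |
|---|---|---|---|
| 0 | 10 | 80% | 70% |
| 10% | 9.5 | 76% | 66% |
| 30% | 8.5 | 68% | 56% |
| 50% | 7.5 | 58% | 46% |

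The 70% in the first row comes from the two-sided assumption, not from partners. At an assumed 80% control prevalence, two-sided power would go from 82% at 10 points to 69% at 8.5 points.

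**5. Type I error.** In a simulation with within-couple correlation 0.5 and a two-sided 5% test that ignores pairing, individual allocation gave 4.8%, 4.8% and 5.1% at c = 25%, 50% and 100%, because same-arm and split pairs offset each other. Couples kept together but analysed as individuals gave 6.5%, 8.2% and 11.3%.

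**6. Cost of allocating couples as units.** The design effect is about 1 + c·ICC. At c = 30% and ICC = 0.5 (both assumed) it is 1.15; 305 × 1.15 = 350.75 completers, and dividing by 0.5 gives 702 enrolled per arm against 610.

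**The case against.** The strongest reply is that this calls for clarification and does not show a loss. Partners are only invited, none of the four recruitment routes runs through a partner, sessions are individual, and no partner-specific assessment is described. Uptake may be low: at c = 10% even the worst case costs about four percentage points of power. The Randomization section names the software but no unit, and the full protocol is not shown.

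That limits the size but does not remove the point. The article itself opens enrolment to both partners and describes the sample only in individuals, to be "which will be randomly and evenly divided between the experimental and control groups". Followed as written, this splits couples.

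A reader might infer four stronger claims that the documents do not support:

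- *Half of all participants are affected.* The 50% concerns only couples in which both members enrol.
- *The effect is necessarily biased towards zero.* If partners' effects add, the average contrast is preserved.
- *A split couple gives a zero contrast whatever the true effect.* That needs perpetration and victimization to be summed and partners to agree fully in their reports. The article lists the two as outcomes and defines no sum.
- *The planned tests produce too many false positives.* Under individual allocation the naive test stays near 5%. Standard errors become too small only if couples share an arm and are analysed as individuals, which the article does not describe.

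**Conclusion.** The point holds as a gap in the unit of randomisation with a bounded consequence. As written, about half of the couples in which both members enrol would be divided between the arms while reporting on the same relationship, so the arms interfere on the primary outcomes. The cost lies between no dilution and a contrast multiplied by (1 - c/2). The lower bound assumes that the benefit is fully shared and that treating the second partner adds nothing. The power figures also rest on an assumed 50% control prevalence and on 305 completers per arm, and c is unknown. Individual allocation is itself inferred, though no other reading has support in the text. Even with no dilution, the estimate would mix couples with one, both and neither member treated, and the article does not say which effect is meant.

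**What to change.** Settle the unit in Participants and design and in Randomization, by one of two routes.

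**(a) One member per couple.** Randomise and analyse only one member of each couple. Cost: fewer eligible recruits.

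**(b) The couple as the unit.** Link partners at registration, for example with a code, and allocate each linked couple once; participants without an enrolled partner are randomised singly. Linking should preferably be complete before the first partner's arm is revealed. If the second partner simply inherits a known arm, that allocation is predictable and the decision to enrol can depend on it. In Statistical analysis, add couple-clustered standard errors or a couple random effect. Allocating couples together without this step would create the false-positive inflation that individual allocation avoids, so the two changes belong together.

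The cost of (b) is one field and one rule in the software, a clustered analysis, and a design effect of about 1 + c·ICC. That effect should be carried into the stated sample size or power, using a stated range for c and ICC. The link code must not disclose one partner's answers to the other.

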#### Randomization

The randomization for the experimental and control group will be performed after the eligibility evaluation, the express agreement to participate in the intervention through the consent form, and the baseline evaluation. The placement into one group or the other will be performed automatically by the *TailorBuilder* software, as has been done before in other similar interventions [45, 46].

#### Recruitment

Several strategies will be used to advertise SOS Dating and recruiting participants: (a) posting on the social networks of social movements related to fighting violence against women, LGBT rights, and youth engagement; (b) advertising on e-mail lists of research associations and research groups interested in related topics; (c) informing the Federal District Ministry of Education, which is connected to public schools frequented by the target audience; and (d) communicating it to student health and guidance services of Brazilian public universities.

